**Figure 1 F1:**
[figure not shown]
CCTA hybrid image which illustrates the coronary tree revealing a severe stenosis in the medial segment of LAD fussed with 3D motion map indicating hypokinesis in the territory of the stenotic artery. LAD = left anterior descending.

### Study time

2.7

The FUSE Heart study will be conducted in a period of two years, from January 2021 to December 2022.

### Outcomes

2.8

The primary outcome of the study is to evaluate the rate of MACE events related to myocardial ischemia at 1-year post assessment, in correlation with the degree of coronary artery stenosis and myocardial ischemia or viability.^[20]^

The study secondary objective is to investigate the correlation between morphology and composition of atheromatous plaques located in a coronary artery and myocardial ischemia in the territory irrigated by the same coronary artery.^[20]^

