### Study population

2.3

The study population will include 100 subjects with coronary lesions depicted by CCTA examination. The study population will consist in:

(1)patients with anatomically significant coronary lesions (at least 50% luminal narrowing) on native coronary arteries, or(2)patients surviving an acute myocardial infarction, revascularized or not.

In all patients, presence of vulnerability features in the atheromatous plaques will be studied and the vulnerability score will be calculated for each plaque, consisting in one point added for each of the following vulnerability markers: positive remodeling, napkin-rink sign, presence of low-density plaque or spotty calcium within the plaque. In addition, following 3D fusion of the images of the coronary tree with the images reflecting wall motion, the correspondence between plaque morphology and composition on one hand, and wall motion in the corresponding distribution territory of that coronary artery, will be studied based on fused models.^[20]^

The study will be conducted over a period of 2 years. Patient assessment will be performed at baseline and at 1 year, and the projected recruitment period will be 1 year.

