**Inclusion criteria:**

Subjects undergoing CCTA examination, with at least one coronary artery lesion producing a luminal narrowing > 50%Conscious subjects in order to sign and assume a paper-based consentSubjects at the age of maturity

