### Participation timeline

2.9

Baseline (day 0)

Acquire and record a written consent from the subjects on customized paper fileConfirm if the subjects meet the inclusion/exclusion criteria.Record demographic data, medication use history, tobacco and alcohol use history.Obtain data regarding physical examinations and 12-lead Electrocardiography recording.Collect blood samples (CBC, biochemistry, NT-proBNP, and inflammatory markers).CCTA acquisition, perform 2 D EchocardiographyImage postprocessing – quantification of coronary stenosis, characterization of vulnerability markers, 3D reconstruction, extension and characterization of wall motionDeliver fused 3D images

Visit 1 (month 1,3,6,12)

Obtain results of physical examinations, 12-lead electrocardiogram (ECG) and medical history.MACE assessment

Final study visit (month 12)

Obtain results of physical examinations and medical history,12-lead ECG recordingPerform transthoracic 2-Dimensional cardiac ultrasoundEnd-point and MACE evaluation.^[20]^

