### Statistical analysis

2.11

The Graph Pad InStat 3.10 software will be used for statistical analysis, with a 5% level of significance. All data will be first checked for normality test. Continuous variables having normal distribution will be considered as mean ± standard deviation and will be compared using the t-test. Non-normally distributed data will be analyzed using the Mann-Whitney test. All the categorical variables, expressed in numbers and percentages, will be compared using the Fisher exact test.^[20]^

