Location of coronary lesions may also play a significant role on the clinical outcomes, since it has been demonstrated that an increased shear stress at the level of coronary bifurcations may accelerate the plaque vulnerabilisation process,^[25]^ while location in the proximal left anterior descendant artery is association with an increased risk of cardiac arrest.^[26]^

The FUSE-HEART study seeks to validate the usefulness and efficacy of fusion imaging by integrating anatomic information provided by CCTA with functional information provided by the same techniques, in order to identify the impact of a stenosis on subjacent myocardial contractility. In the case of multivessel disease, this fusion imaging may help to understand the complex interaction between different myocardial areas irrigated by stenotic arteries of the same heart.

At the same time, the impact of a coronary lesion results not only from its anatomical severity, but also from its composition. It has been demonstrated that vulnerable plaques triggering an acute cardiac event exhibit a different CCTA phenotype than plaques that remain un-ruptured. In a recent study by Licu et al, the most relevant vulnerability markers associated with an acute coronary event were presence of low attenuation within the plaque (*P* < .0001) and positive remodeling (*P* < .0001), while low attenuation plaques was the strongest independent predictor of acute myocardial infarction at 6 months (OR 8.18 [1.23–95.08], *P* = .04).^[27]^ Systemic inflammation may play also a significant role in the complex process of plaque vulnerabilisation and also in the evolution in the period of time post myocardial infarction^.^^[28,29]^ Therefore, the FUSE-Heart study will include a biomarker sub-study in order to investigate the association between systemic vulnerability and local factors that favor plaque vulnerabilisation, as well as the reflection of this association on plaque vulnerabilisation at a local level.

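### The tests named for the secondary objective cannot hold a lesion's own stenosis constant, so a plaque-composition finding can reflect stenosis severity instead

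*Protocol article*

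**What the plan says.** Sections 1.2 and 2.8 of the protocol article give the secondary objective as the "correlation between morphology and composition of atheromatous plaques located in a coronary artery and myocardial ischemia", with ischemia assessed where that artery supplies the heart. Section 2.3 makes this operational: the fused images will be used to study "the correspondence between plaque morphology and composition on one hand, and wall motion in the corresponding distribution territory of that coronary artery", and a vulnerability score is calculated for each plaque.

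Section 2.8 names stenosis as a correlate only for the primary outcome, where the MACE rate is taken "in correlation with the degree of coronary artery stenosis and myocardial ischemia or viability". Section 2.1 is broader. It puts stenosis severity, plaque composition and ischemia together as the relation to be studied, but attaches no method.

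Stenosis is measured. The baseline post-processing step in section 2.9 covers "quantification of coronary stenosis, characterization of vulnerability markers" and wall motion. Severity also varies in the sample, because the inclusion criterion is "at least one coronary artery lesion producing a luminal narrowing > 50"%, with no upper limit.

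Section 2.11 gives the analysis. Normally distributed continuous variables "will be compared using the t-test", non-normal ones are compared by Mann-Whitney, and categorical ones by Fisher's exact test. It names no regression, stratification, matching or correlation method.

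The Discussion gives the rationale: "the impact of a coronary lesion results not only from its anatomical severity, but also from its composition".

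**The concern.** The question in section 2.1 has three variables, and every named test handles two. The trial's own working hypothesis is that stenosis impairs the myocardium it supplies: this is the primary objective, and the Figure 1 caption describes a severe stenosis with hypokinesis in its territory. If tighter lesions also tend to carry more vulnerability features, composition and wall motion will be associated even when composition does nothing by itself.

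At stake is how a positive secondary result can be read. The rationale is that composition counts in addition to anatomical severity. A comparison that ignores severity cannot separate that from severity alone. The point concerns the lesion-level secondary question only. It does not touch the MACE comparison or the mix of infarct and non-infarct patients.

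**Working it through.** **The plan's own figure.** The article gives no power or error figure for the secondary objective. Its one such figure is for MACE-free rates: 50 per group, 0.60 against 0.60 + 0.29 = 0.89, two-sided alpha 0.05, power 90%. The exact power of Fisher's test with these inputs is 90.2%, so the figure reproduces. It is not in dispute here.

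**Inputs for the check.** From the article: 100 subjects, a 5% significance level, unadjusted tests. Assumed, because the article gives no values:
- one independent lesion per subject, so n = 100;
- no direct effect of composition on wall motion;
- correlation *a* between stenosis and the vulnerability score;
- correlation *b* between stenosis and territory wall motion.

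**Formula.** With no direct effect, the unadjusted correlation between score and wall motion is r = a × b. Splitting the score at its median for a t-test shrinks this by √(2/π) = 0.798. The approximate rejection rate is Φ(m − 1.96) + Φ(−m − 1.96), with m = atanh(r) × √(n − 3) and √97 = 9.849. The article fixes neither a median split nor a correlation test. Both are shown because section 2.11 names the t-test and section 2.8 speaks of a correlation.

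**Example, a = b = 0.5.** r = 0.25 and m = 0.2554 × 9.849 = 2.52, so a correlation test rejects 71% of the time. For the median-split t-test, r = 0.25 × 0.798 = 0.1995 and m = 1.99, which gives 51%.

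| a / b | r = a × b | t-test, median split | correlation test |
|---|---|---|---|
| 0 / 0.5 | 0 | 5% | 5% |
| 0.2 / 0.2 | 0.04 | 6% | 7% |
| 0.2 / 0.3 | 0.06 | 8% | 9% |
| 0.3 / 0.3 | 0.09 | 11% | 14% |
| 0.4 / 0.5 | 0.20 | 35% | 51% |
| 0.5 / 0.5 | 0.25 | 51% | 71% |

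Simulation of the same model agrees within simulation error: 11% to 52% for the t-test and 15% to 72% for the correlation test over 0.3 to 0.5. With stenosis held constant the rate is about 5% throughout.

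**A second model.** Here stenosis is uniform from 50% to 100%, 40% of lesions have a high-risk plaque feature, and 40% of territories have abnormal wall motion. Each setting had 2,000 runs. Mann-Whitney compares the underlying continuous wall-motion value.

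| a / b | Fisher | Mann-Whitney | stenosis in the model |
|---|---|---|---|
| 0 / 0.5 | 3.7% | 5.1% | 5.3% |
| 0.2 / 0.3 | 5.6% | 8.2% | 6.0% |
| 0.3 / 0.5 | 13.0% | 20.8% | 4.5% |
| 0.4 / 0.5 | 21.2% | 34.2% | 4.0% |
| 0.5 / 0.5 | 34.4% | 50.7% | 4.9% |

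More lesions make it worse. With 200 independent lesions at 0.5/0.5, Fisher rejects 64.2% and Mann-Whitney 83.2% of the time, against 4.5% with stenosis in the model.

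**The case against.** The strongest reply is that section 2.11 is a short general paragraph that ties no test to the secondary objective, and that an article may leave the lesion-level model to a fuller document. That is fair as far as it goes: the article does not state that stenosis will be ignored, and section 2.1 names it in the aim. But the article is not silent on method. It lists its tests, and none of them can hold stenosis constant.

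Four further objections stand and limit the point.

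- A reader might infer that a severity effect *will* be reported as a composition effect. The documents do not support this. They give neither correlation, and if stenosis and composition are uncorrelated there is no inflation. The entry criterion above 50% restricts the range of severity, and section 1.1 notes that anatomical significance and ischemia do not always go together. Both leave room for weak correlations.
- A reader might take the Discussion sentence on severity and composition as the study's stated conclusion. It is background rationale. The objective as worded claims only a correlation, and an unadjusted analysis can describe that.
- Stenosis may lie partly on the path from plaque to ischemia. Adjustment then removes part of the total effect, so the adjusted estimate should govern only claims beyond severity.
- The article does not list proximal or distal position as a recorded variable, and patients with multivessel disease can contribute several lesions. A model should not presume the first and must allow for the second.

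**Conclusion.** The concern holds in a limited form. The unadjusted tests in section 2.11 do not match the three-variable aim in section 2.1, and a positive composition result from them can be due to the same lesion's stenosis. With 100 independent lesions and no direct composition effect, the false-positive rate of an unadjusted t-test or correlation test runs from the nominal 5% (no stenosis-composition correlation), through 6% to 9% (correlations 0.2/0.2 to 0.2/0.3), to 11% to 72% (both between 0.3 and 0.5). Adjustment brings it to about 5%. All these correlations are assumptions, so the figures show what is possible and do not predict this study's result. The primary outcome and its sample size are unaffected. The change should be made because it is cheap and bears directly on how the secondary result can be read.

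**What to change.** In section 2.11, for the secondary objective, add a lesion- or territory-level regression of wall motion on the vulnerability score, and on its individual markers. Include the same lesion's percent stenosis as a continuous covariate, and the vessel. Allow for several lesions per patient with cluster-robust standard errors or a mixed model.

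Report unadjusted and adjusted estimates side by side. Base any statement that composition matters beyond anatomical severity on the adjusted estimate. The unadjusted one may still be described as a plain correlation.

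The cost is a wording change and somewhat more analysis work. No new data or visits are needed: stenosis, plaque markers and wall motion come from the same baseline post-processing, and the vessel is known because each territory is assigned to its artery. The interval widens slightly. At a score-stenosis correlation of 0.4 the standard error rises by a factor of 1/√(1 − 0.16) = 1.09, about 9%, with residual variance held fixed.

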### Participation timeline

2.9

Baseline (day 0)

Acquire and record a written consent from the subjects on customized paper fileConfirm if the subjects meet the inclusion/exclusion criteria.Record demographic data, medication use history, tobacco and alcohol use history.Obtain data regarding physical examinations and 12-lead Electrocardiography recording.Collect blood samples (CBC, biochemistry, NT-proBNP, and inflammatory markers).CCTA acquisition, perform 2 D EchocardiographyImage postprocessing – quantification of coronary stenosis, characterization of vulnerability markers, 3D reconstruction, extension and characterization of wall motionDeliver fused 3D images

Visit 1 (month 1,3,6,12)

Obtain results of physical examinations, 12-lead electrocardiogram (ECG) and medical history.MACE assessment

Final study visit (month 12)

Obtain results of physical examinations and medical history,12-lead ECG recordingPerform transthoracic 2-Dimensional cardiac ultrasoundEnd-point and MACE evaluation.^[20]^

**Study procedures:**

Medical history evaluation, clinical examination, laboratory tests assessment which consist of (complete blood count, biochemistry, inflammatory biomarkers: hs-CRP, MMP, interleukin 6, and N-terminal prohormone of brain natriuretic peptide)

12-lead ECG

2D transthoracic echocardiography

CCTA

Computerized postprocessing and fused images

**Data collection**: All data will be recorded in a dedicated databank including medical history data, medication use history, imaging features provided by cardiac ultrasound, CCTA and fused images resulting from imaging post-processing.^[20]^ FUSE-HEART flowchart is presented in Figure 2.

**Figure 2 F2:**
[figure not shown]
Illustrates the FUSE-HEART (FH) diagram with the flowchart that will be used in the study.

### Sample size

2.10

The trial sample size is represented by 100 subjects with anatomically significant coronary artery disease depicted by CCTA examination. The lot size estimation was done using the StatMate 2.0 software. A percent of 60% event-free study population was estimated for sample size calculation%, and a sample size of 50 subjects in each group is associated with a power of 90% for detection of an increase of 0.29 in MACE-free rates proportion, with a significance level (alpha) of 0.05 (two-tailed). Consequently, the study lot population including the 2 study groups of 50 patients each, was set at 100 patients.

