### Study groups

2.5

One hundred subjects meeting the selection criteria will be divided into 2 groups, thus, subjects with anatomically significant coronary lesions (at least 50% luminal narrowing) on native coronary arteries (group 1), and subjects surviving an acute myocardial infarction, revascularized or not (group 2).^[20]^

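### The 90% power in section 2.10 belongs to a comparison of the two clinical groups; the association that forms the primary outcome has no stated power

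*Protocol article*

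**What the plan says.** Section 2.10 (Sample size) starts from a rate: "A percent of 60% event-free study population was estimated for sample size calculation". It then states that "a sample size of 50 subjects in each group is associated with a power of 90% for detection of an increase of 0.29" in the MACE-free proportion, at a two-sided 5% level, and concludes that "the study lot population including the 2 study groups of 50 patients each, was set at 100 patients".

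Section 2.5 (Study groups) says that "One hundred subjects meeting the selection criteria will be divided into 2 groups". Group 1 has anatomically significant lesions on native coronary arteries. Group 2 has survived an acute myocardial infarction. Section 2.3 gives the same two categories, and no other grouping is defined.

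Section 2.8 (Outcomes) makes the primary outcome the 1-year rate of ischemia-related MACE, taken "in correlation with the degree of coronary artery stenosis and myocardial ischemia or viability". The abstract says the same. The objectives in section 1.2 concern the effect of stenosis on myocardial function and viability, and the relation of plaque features to ischemia. None of them asks whether the two clinical groups differ in MACE.

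The inclusion criteria in section 2.3 require every subject to have at least one lesion narrowing the lumen by more than 50%.

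**The concern.** Power belongs to a particular contrast, not to an endpoint. Sections 2.10 and 2.8 share the endpoint, 1-year MACE, but differ in what it is set against: clinical group in 2.10, and stenosis with ischemia or viability in 2.8.

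The groups cannot stand in for those factors. All subjects exceed the same stenosis threshold, so the groups do not separate high from low stenosis, and neither group is defined by ischemia or viability. A difference in MACE between them would show that a previous infarction marks a different risk. It would not show that stenosis, ischemia or viability predicts events.

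Two misreadings are at stake. A group 1 versus group 2 result could be taken as the powered main finding although it does not address the primary outcome. A null association between MACE and the imaging factors could be taken as coming from a study with 90% power to find it.

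**Working it through.** **Inputs from section 2.10:** 50 per group, two-sided alpha 0.05, MACE-free proportion 0.60, increase 0.29 (so 0.60 versus 0.89), stated power 90%. Section 2.11 names the Fisher exact test for categorical data.

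**Step 1: reproduce the stated figure.**

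- Fisher exact: power = Σ Bin(i; 50, 0.60) × Bin(j; 50, 0.89), summed over all tables (i, j) with Fisher p ≤ 0.05. Result: **90.2%**.
- Normal approximation with pooled variance under the null: p̄ = (0.60 + 0.89)/2 = 0.745. Null SE = √(2 × 0.745 × 0.255/50) = 0.0872. Alternative SE = √((0.60 × 0.40 + 0.89 × 0.11)/50) = 0.0822. z = (0.29 − 1.96 × 0.0872)/0.0822 = 1.45, so power is 92.6%.
- The same with continuity correction (subtract 1/50 = 0.02 from the difference): z = 1.21, power 88.6%.

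The 90% reproduces as a two-group contrast with 0.60 as the reference rate. Other readings do not give it: 60% as the overall rate (0.455 versus 0.745) gives 81% by Fisher, and a decrease from 0.60 to 0.31 gives 80%.

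**Step 2: would the 90% carry over to a binary ischemia or viability marker?** Keep 0.60 versus 0.89 and 100 patients, and vary the share who have the marker. The article gives no prevalence, so these splits are assumptions. Fisher exact power follows; the range depends on which side is the smaller.

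| Split of 100 | Power |
|---|---|
| 50/50 | 90% |
| 40/60 | 90–91% |
| 30/70 | 84–86% |
| 20/80 | 71–79% |
| 10/90 | 40–57% |

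With an even split but a smaller (assumed) difference from 0.60, power is 76% for 0.25, 52% for 0.20, 29% for 0.15 and 13% for 0.10.

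**Step 3: stenosis degree as a continuous predictor.** Assume a logistic model on n = 100 with overall MACE rate P. The odds ratio per SD detectable with 90% power is exp[(1.960 + 1.282)/√(n P (1 − P))].

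- P = 0.40 (60% read as the whole cohort's event-free rate): exp(3.242/√24.0) = **1.9**
- P = 0.255 (average of 0.40 and 0.11): exp(3.242/√19.0) = **2.1**
- P = 0.11 (the lower of the plan's two implied rates, applied to everyone): exp(3.242/√9.79) = **2.8**

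An assumed odds ratio of 1.5 per SD would have 51%, 42% and 24% power respectively. The exponents (0.66, 0.74 and 1.04) are also, by the same normal approximation, the mean differences in SD units needed for 90% power when patients with and without MACE are compared by the t-test of section 2.11.

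**The case against.** **The article condenses a fuller plan, and an SAP may define the primary analysis.** It may, and missing modelling detail is not the point here. Section 2.10 prints a sample-size basis that does not match the primary outcome in section 2.8, and no separate document can make that 90% refer to a different contrast. It is fair to add that section 2.10 never claims the 90% applies to the imaging association. What can be said is that this association has no stated power.

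**The odds ratios come from a model the plan does not contain.** This is correct. Section 2.11 lists only the t-test, the Mann-Whitney test and the Fisher exact test. The logistic figures are illustrations under stated assumptions, although the t-test leads to the same requirement on another scale.

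**This is an observational cohort.** No treatment allocation or decision rule hangs on the calculation. That limits the consequences to what the study may conclude; it does not remove the mismatch.

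A reader might infer three stronger things, none of which the article supports:

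- *That the study is underpowered for its primary outcome.* The article gives no effect size for stenosis, ischemia or viability, so this cannot be established. With a near-even marker split and a true 0.29 difference, power would be about 90%.
- *That there are three interchangeable predictors.* Section 2.8 joins only ischemia and viability by an 'or'. Section 1.1 discusses viability mainly after infarction and functional significance in patients without infarction, so the 'or' may follow the two groups, though the article does not say so.
- *That the type I error is inflated by three tests.* No section plans three separate tests at 5%, and the handling of several factors is commonly left to an SAP.

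**Conclusion.** The mismatch between sections 2.10 and 2.8 stands. The stated 90% is correctly computed, but for a comparison that no objective or outcome asks for. It would describe the primary outcome only if an ischemia or viability marker split the cohort roughly evenly with MACE-free rates near 0.60 and 0.89, and the article states neither condition.

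How far the true power departs from 90% is unknown, so no single corrected figure exists. The ranges in the working rest on assumed marker prevalences, assumed effect sizes and, for the continuous case, an assumed unadjusted logistic model. They show that the 90% is sensitive to conditions the plan leaves unstated.

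**What to change.** - **Section 2.10:** state that the 90% power for a 0.29 difference applies only to group 1 versus group 2, and label that comparison descriptive. Add the effect that 100 patients can detect for the association in section 2.8, showing the assumed event rate and, for a binary factor, the assumed prevalence.
- **Section 2.8:** state which of the factors already named there (stenosis degree, ischemia or viability) is the primary predictor, analysed across all 100 patients with stratification by group, so that the effect of prior infarction is not mistaken for that of the predictor. If ischemia is meant for one group and viability for the other, say so, and work out the detectable effect on 50 patients for each.

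The cost is protocol and SAP wording, with no new procedures. The downside is that the stated power becomes less favourable. Whether 100 patients are enough can be judged only once the sponsor states a plausible effect for the chosen predictor.
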